### Objectives {7}

The objective of this trial is to determine whether the maintenance of a low intraperitoneal insufflation pressure (IIP) of ≤10 mmHg during the parenchymal transection phase of conventional and robotic-assisted laparoscopic liver resections is non-inferior to a higher IIP of ≥14 mmHg in terms of intraoperative blood loss, gas embolisms, perioperative morbidity, and mortality.

The primary research question is as follows: Is the maintenance of a low IIP of ≤10 mmHg during the parenchymal transection phase of conventional or robotic-assisted laparoscopic liver resections non-inferior to a higher IIP of ≥14 mmHg in terms of intraoperative blood loss during the parenchymal transection phase?

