### Trial design {8}

This study is a two-arm parallel-group, randomized non-inferiority trial in patients undergoing elective minimally invasive liver surgery with an allocation ratio of 1:1 per hospital and a follow-up period of 3 months. The flow diagram of the study is presented in Fig. 1.

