### Criteria for discontinuing or modifying allocated interventions {11b}

Individual withdrawal criteria will include the participant’s right to withdraw consent at any time without any negative consequences for their subsequent medical care. Participants may choose to withdraw if they experience adverse events or if they feel uncomfortable continuing in the study for any reason. Additionally, any significant changes in their medical condition that may affect their safety or the validity of the trial, such as newly diagnosed medical conditions or complications related to the surgical procedure, may also warrant withdrawal from the study. The research team will ensure that participants are fully informed of their right to discontinue their participation at any point during the trial, and efforts will be made to document the reasons for withdrawal if disclosed.

Withdrawal criteria for the overall PPULS trial may arise from significant changes in the safety landscape during the study period, such as emerging data that indicate an unacceptable level of risk for participants. This could include new findings related to the incidence of adverse events associated with the pneumoperitoneum pressures being tested, or if there are changes in clinical guidelines that recommend against the studied interventions. This trial will be discontinued only for reasons pertaining to efficacy, safety, or feasibility. However, at this stage, no specific overall withdrawal criteria have been identified; the study is designed with appropriate monitoring and safety protocols in place to ensure participant welfare throughout its duration.

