### Strategies to improve adherence to interventions {11c}

Not applicable as the intervention is performed during surgery.

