#### Secondary outcomes

The secondary endpoints of the study are defined as follows:Intraoperative blood loss in milliliters measured during the overall surgical procedure (from first skin incision to full skin closure)Incidence of CO_2_ embolisms in the right atrioventricular system detected by intraoperative transesophageal echocardiography with a mid-esophageal right ventricular inflow-outflow (RVOT) view before, during, and after the parenchymal transection phase. The occurrence of CO_2_ embolisms will be graded according to the “Tübingen Venous Air Embolism Grading Scale” [15]Other surgery-related secondary endpoints include:The quality of the surgical field (L-SRS)The overall time of surgery and the duration of the parenchymal transection phase in minutesIIP at the end of the parenchymal transection phase and mean IIP outside of the parenchymal transection phase, number of surgeries with an increase of +2 mmHg, +4 mmHg, or +6 mmHg, etc.Occurrence of intraoperative surgical complications other than gas embolismConversion rate to open laparotomyDifficulty of liver resection according to the “scoring system for laparoscopic liver resection”Indocyanine green (ICG) clearance after the parenchymal transection phase and 24 h laterOther anesthesia-related secondary outcomes include:Application of perioperative peridural catheter (drug, dosage, duration)Mean dose of narcotic drugs (propofol, sufentanil, remifentanil, lidocaine, esketamine, rocuronium, cisatracurium, and others)Transfusion rate and coagulation factor administrationNeuromuscular blockade reversal (sugammadex and others)Usage of vasopressors (epinephrine, noradrenaline, dobutamine, theodrenaline-cafedrine, and others)Use of buffer solutions (natrium bicarbonate and tris(hydroxymethyl)aminomethane)Mean EtCO_2_ and occurrence of an abrupt end-tidal carbon dioxide (EtCO_2_) partial pressure decrease ≥5 mmHg and mean arterial carbon dioxide pressure (paCO_2_), pH and bicarbonate at 15-min intervals during the parenchymal transection phase and every 30 min outside of itA sudden decrease in MAP > 20 mmHgAbnormal regional cerebral oxygen saturation (rScO_2_) (defined as a decrease in rScO_2_ > 15% compared with baseline or rScO_2_ < 50%)Mean central venous pressure (CVP) and increased CVP (CVP > 10) at 15-min intervalsPeripheral oxygen saturation (SpO_2_) <90%, or changes in SpO_2_ or hypoxia (SpO_2_ < 90% lasting at least 1 min)Heart rate (HR)Mean arterial pressure (MAP) and hypotension (MAP < 65 mmHg)Arterial lactateVentilation parameters: mean positive end expiratory pressure (PEEP), inspiratory pressure (Pinsp), mean airway pressure (Pmean), breathing ratePerioperative fluid balancePostoperative secondary outcomes include:Surgery-related postoperative complications (e.g., wound impairments, biliary leakage, postoperative liver failure, pulmonary complications)Overall postoperative morbidity within 30 postoperative days measured via the Comprehensive Complication Index (CCI) [16] according to the Clavien-Dindo classification [17]Dose of postoperative opioid analgesics (piritramide and others) and dose of postoperative non-opioid analgesics (metamizole, paracetamol, and others) for 48 h after the surgeryPostoperative laboratory values (e.g., bilirubin, c-reactive protein (CRP), international normalized ratio (INR))Length of the intensive care unit (ICU) stays, readmissions to the ICU, and overall hospital stayNausea and vomiting, use of emetic medications, day of first postoperative bowel movement, use of prokinetic medicationsQuality of recovery based on the Quality of Recovery 40 (QoR-40) questionnaire on postoperative days 1, 3, and 7Histopathology outcomes (e.g., lymph node yield, perineural and lymphovascular invasion)Postoperative neurological recovery according to the National Institutes of Health Stroke Scale (NIHSS)Outcomes assessed during follow-up include:30-day and 90-day survival.Hospital readmission within 30 days of remission.In case of a malignant diagnosis, oncologic outcome (overall survival and disease-free survival) will be evaluated based on [18] surgical margins (R0—no evident tumor along the transection surface or within 1 mm of it; R1—microscopically positive; R2—grossly positive).To assess the effect of pneumoperitoneum pressure on tissue damage:Plasma damage-associated molecular patterns (DAMPs), for example, heat shock protein 70 (HSP70), high mobility group box 1 (HMGB1), nuclear deoxyribonucleic acid (nDNA), and mitochondrial DNA (mtDNA).Plasma cytokines (for example, tumor necrosis factor alpha (TNFα), interleukin-10 (IL-10), and IL-6) will be evaluated from blood samples drawn directly before the parenchymal phase and at the end of it, as well as on postoperative days 1 and 3.In addition, liver and peritoneal biopsies will be taken before and after the parenchymal transection phase of the liver resection. Biopsies will be used to extract mRNA and determine:Levels of hypoxia-inducible factor 1-alpha (HIF1α), TNFα, IL-1β, IL-6, vascular endothelial growth factor (VEGF), hepatocyte growth factor (HGF), and platelet-derived growth factor (PDGF).

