### Confidentiality {27}

Medical confidentiality and data protection regulations will be strictly observed. During the study, medical findings and personal information about the participants will be collected and recorded either in a personal file at the study site or electronically stored. Data relevant to the study will additionally be stored in a pseudonymized form. The study management will take all reasonable measures to protect the data in accordance with the European Union’s data protection standards. The data will be secured against unauthorized access, and decoding will occur only in case of withdrawal from the study and data destruction is required.

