### Methods in analysis to handle protocol non-adherence and any statistical methods to handle missing data {20c}

For the primary analysis, a complete-case analysis will be performed, considering only patients with complete data. Missing data will not be imputed unless the proportion of missing data is determined to be significant. Additionally, a multiple imputation method will be employed as a sensitivity analysis to assess the robustness of the results in the presence of missing data and to minimize potential bias from non-randomly missing values.

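### Surgical complications are a stated reason for withdrawal from the study, which can end follow-up in patients selected because they had an outcome event

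*Protocol article*

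**What the plan says.** Section {11b} of the protocol article gives two routes out of the trial for an individual. The first is the participant's right to withdraw consent at any time. The second is a significant change in medical condition that may affect the patient's safety or the validity of the trial; changes "such as newly diagnosed medical conditions or complications related to the surgical procedure, may also warrant withdrawal from the study". What follows is departure from the study, not only from the allocated pressure.

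Other sections bear on this:

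- **Intervention.** Section {11a} confines the difference between arms to the transection phase. Section {11c}, on adherence, reads "Not applicable as the intervention is performed during surgery".
- **Objective.** Section {7} frames non-inferiority "in terms of intraoperative blood loss, gas embolisms, perioperative morbidity, and mortality".
- **Outcomes.** Section {12} lists intraoperative complications other than gas embolism, "Surgery-related postoperative complications (e.g., wound impairments, biliary leakage, postoperative liver failure, pulmonary complications", and "Overall postoperative morbidity within 30 postoperative days measured via the Comprehensive Complication Index (CCI". It also lists ICU and hospital stay, QoR-40 to day 7, readmission, and 30- and 90-day survival.
- **Follow-up.** Section {8} sets "a follow-up period of 3 months". Section {18b} builds it into routine care without extra visits.
- **Analysis sets.** In section {20a} the safety analysis covers everyone treated under either pressure. The mITT set depends on the intervention having been started and on the intraoperative criteria being met.

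**The concern.** A withdrawal criterion normally protects a patient from further exposure to an allocated treatment. Here exposure is over when transection ends. What remains is mostly observation: questionnaires, blood samples, recovery at discharge and a telephone interview at 3 months. Withdrawing a patient for a postoperative complication therefore removes little besides data.

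The patients removed would not be a random subset. They would be selected because they had an event that the trial counts. Complicated patients are also those in whom a high 30-day complication index, a long stay, readmission, poor QoR-40 scores or death by day 90 are most plausible. Morbidity and mortality are part of the stated non-inferiority objective, and a loss that makes the arms look more alike is not conservative in such a trial.

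**Working it through.** **1. Sections side by side.** The trigger in {11b} is a complication of surgery. The outcomes in {12} include complications of surgery and their later consequences. The intervention in {11a} is over before any postoperative complication can occur. For a postoperative complication, then, the clause has no treatment to stop and acts only on follow-up.

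**2. What is exposed and what is not.**

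| Item | When observed | Exposed? |
|---|---|---|
| Blood loss during transection (primary) | In theatre | Only if withdrawal comes before or during transection |
| The complication that triggers withdrawal | Before withdrawal | Little, if recorded: section {22} has SAEs on a CRF form and reported within 24 h |
| 30-day complication index, stay, QoR-40, readmission, 90-day survival | After many complications | Yes |

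**3. Form of the bias.** Let r be the share of an arm with a complication and w the share of those who are withdrawn. The share lost is q = r × w. For any later outcome,

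true value − observed value = q × (value in the withdrawn − value in the retained).

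The bias is zero if the two groups have the same later outcome. Because complications select the withdrawn, equality is not to be expected.

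**4. Illustration.** The article gives neither r nor w, so both are assumptions. The only planned figure nearby is the 5% loss to follow-up in section {14}: 0.05 × 66 = 3.3 patients per arm.

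- r = 20%, w = 25%: q = 0.20 × 0.25 = 5%, and 66 × 0.05 = 3.3 patients, the whole allowance.
- Over r = 20% to 40% and w = 10% to 50%: q runs from 2% to 20%, that is 1.3 to 13.2 patients per arm.

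**5. Outer case.** Suppose the triggering complication were itself lost and rates were taken in retained patients. The observed rate would be r(1 − w)/(1 − rw).

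| True r | w = 10% | w = 25% | w = 50% |
|---|---|---|---|
| 20% | 18.4% | 15.8% | 11.1% |
| 30% | 27.8% | 24.3% | 17.6% |
| 30% vs 20% (10 points) | 9.5 points | 8.5 points | 6.5 points |

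Check at r = 20%, w = 25%: 0.05 × (100% − 15.8%) = 4.2 points, which is 20% − 15.8%. This case shows the mechanism. It is not an estimate, because it deletes an event that the article has recorded before withdrawal.

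**6. Direction between arms.** Equal withdrawal shrinks a real difference, as in the last row. Unequal withdrawal can create one: with a true 30% in both arms and 0% against 25% of complicated patients withdrawn, the rates are 30% and 24.3%, a false 5.7 points. Equal withdrawal cannot be taken for granted, since anesthesiologists and coordinators know the allocation.

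**The case against.** Several points on the other side stand.

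- **Recorded events stay.** A reader might infer that a complication leading to withdrawal disappears from the results. The article does not support that. Neither the safety set nor the mITT set requires study completion, SAEs are documented at once, and the complication is known before the withdrawal it causes.
- **Data destruction.** A reader might take "decoding will occur only in case of withdrawal from the study and data destruction is required" in section {27} to mean that withdrawn patients' data are deleted. The sentence only says when pseudonymized data may be decoded, and it needs both conditions together. It does not make deletion follow from withdrawal.
- **Complete cases.** Section {20c} says "a complete-case analysis will be performed, considering only patients with complete data", but for the primary analysis, with multiple imputation as a sensitivity analysis. It does not extend the rule to morbidity or survival.
- **The primary result.** A reader might infer that the largest blood losses drop out and tilt the trial toward non-inferiority. That would need withdrawal before or during transection, an unrecorded value and an excess in one arm. The article states none of these.
- **Narrow and permissive wording.** The clause says may, not must, and is limited to changes affecting safety or trial validity. Consent is taken at the outpatient visit and randomization is intraoperative, so a finding in between is a proper reason not to proceed.
- **A condensed article.** Rules on data kept after withdrawal may stand in the full protocol, so their absence here is no defect.

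None of this removes the central difficulty. The article does not merely leave withdrawal undefined: it names complications of surgery as grounds for leaving the study, and in the postoperative period that can only cost follow-up. Imputation would ease the loss but not cure it where missingness depends on the unobserved outcome.

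**Conclusion.** The point holds for later secondary and safety outcomes: the 30-day complication index, length of stay, readmission, QoR-40 and 90-day survival. Section {11b} permits follow-up to end because an outcome event occurred, at a time when no allocated treatment remains to be stopped.

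The size cannot be derived from the documents. It depends on how often complications occur, how often sites use the clause, and how far withdrawn and retained patients differ later. The percentages in the working are assumed. At 20% complications with a quarter withdrawn, the loss would match the planned 5%; if sites never use the clause, there is no loss from this source. The bias can run toward no difference or can create a difference, depending on whether withdrawal is balanced between arms.

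The stronger conclusions, that recorded harms are removed or that the blood-loss comparison is compromised, are not supported. This is a flaw of wording with a real route to bias in secondary outcomes. It is worth correcting while recruitment runs (planned to December 2027), because follow-up not collected may not be recoverable.

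**What to change.** Amend section {11b} as follows:

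1. Remove complications of surgery and newly diagnosed conditions, when they arise after randomization, as reasons for investigator-led withdrawal from the study.
2. Treat departure from the allocated pressure as a separate event. The patient stays in the mITT and safety sets, with data collection and follow-up to 3 months. This concerns data only; when the pressure may be changed is a clinical matter and is left as it stands.
3. Make withdrawal of consent by the participant the only route to ending follow-up, and keep data collected up to that point unless the participant asks for deletion.
4. Leave ineligibility found before randomization, for example at echocardiography or diagnostic laparoscopy, as a reason not to randomize.

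The cost is a change of protocol wording, communicated as section {25} already provides. No visits, patients or measurements are added, since follow-up of these patients is already scheduled within routine care.

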### Strategies to improve adherence to interventions {11c}

Not applicable as the intervention is performed during surgery.

### Relevant concomitant care permitted or prohibited during the trial {11d}

Not applicable as patients receive the best medical care independent of their study participation.

### Provisions for post-trial care {30}

Not applicable as no provisions are available through this trial.

### Outcomes {12}

#### Primary outcome

The primary study endpoint is intraoperative blood loss in milliliters measured during the parenchymal transection phase. It will be referred to as *intraoperative blood loss during the parenchymal transection phase*.

#### Secondary outcomes

The secondary endpoints of the study are defined as follows:Intraoperative blood loss in milliliters measured during the overall surgical procedure (from first skin incision to full skin closure)Incidence of CO_2_ embolisms in the right atrioventricular system detected by intraoperative transesophageal echocardiography with a mid-esophageal right ventricular inflow-outflow (RVOT) view before, during, and after the parenchymal transection phase. The occurrence of CO_2_ embolisms will be graded according to the “Tübingen Venous Air Embolism Grading Scale” [15]Other surgery-related secondary endpoints include:The quality of the surgical field (L-SRS)The overall time of surgery and the duration of the parenchymal transection phase in minutesIIP at the end of the parenchymal transection phase and mean IIP outside of the parenchymal transection phase, number of surgeries with an increase of +2 mmHg, +4 mmHg, or +6 mmHg, etc.Occurrence of intraoperative surgical complications other than gas embolismConversion rate to open laparotomyDifficulty of liver resection according to the “scoring system for laparoscopic liver resection”Indocyanine green (ICG) clearance after the parenchymal transection phase and 24 h laterOther anesthesia-related secondary outcomes include:Application of perioperative peridural catheter (drug, dosage, duration)Mean dose of narcotic drugs (propofol, sufentanil, remifentanil, lidocaine, esketamine, rocuronium, cisatracurium, and others)Transfusion rate and coagulation factor administrationNeuromuscular blockade reversal (sugammadex and others)Usage of vasopressors (epinephrine, noradrenaline, dobutamine, theodrenaline-cafedrine, and others)Use of buffer solutions (natrium bicarbonate and tris(hydroxymethyl)aminomethane)Mean EtCO_2_ and occurrence of an abrupt end-tidal carbon dioxide (EtCO_2_) partial pressure decrease ≥5 mmHg and mean arterial carbon dioxide pressure (paCO_2_), pH and bicarbonate at 15-min intervals during the parenchymal transection phase and every 30 min outside of itA sudden decrease in MAP > 20 mmHgAbnormal regional cerebral oxygen saturation (rScO_2_) (defined as a decrease in rScO_2_ > 15% compared with baseline or rScO_2_ < 50%)Mean central venous pressure (CVP) and increased CVP (CVP > 10) at 15-min intervalsPeripheral oxygen saturation (SpO_2_) <90%, or changes in SpO_2_ or hypoxia (SpO_2_ < 90% lasting at least 1 min)Heart rate (HR)Mean arterial pressure (MAP) and hypotension (MAP < 65 mmHg)Arterial lactateVentilation parameters: mean positive end expiratory pressure (PEEP), inspiratory pressure (Pinsp), mean airway pressure (Pmean), breathing ratePerioperative fluid balancePostoperative secondary outcomes include:Surgery-related postoperative complications (e.g., wound impairments, biliary leakage, postoperative liver failure, pulmonary complications)Overall postoperative morbidity within 30 postoperative days measured via the Comprehensive Complication Index (CCI) [16] according to the Clavien-Dindo classification [17]Dose of postoperative opioid analgesics (piritramide and others) and dose of postoperative non-opioid analgesics (metamizole, paracetamol, and others) for 48 h after the surgeryPostoperative laboratory values (e.g., bilirubin, c-reactive protein (CRP), international normalized ratio (INR))Length of the intensive care unit (ICU) stays, readmissions to the ICU, and overall hospital stayNausea and vomiting, use of emetic medications, day of first postoperative bowel movement, use of prokinetic medicationsQuality of recovery based on the Quality of Recovery 40 (QoR-40) questionnaire on postoperative days 1, 3, and 7Histopathology outcomes (e.g., lymph node yield, perineural and lymphovascular invasion)Postoperative neurological recovery according to the National Institutes of Health Stroke Scale (NIHSS)Outcomes assessed during follow-up include:30-day and 90-day survival.Hospital readmission within 30 days of remission.In case of a malignant diagnosis, oncologic outcome (overall survival and disease-free survival) will be evaluated based on [18] surgical margins (R0—no evident tumor along the transection surface or within 1 mm of it; R1—microscopically positive; R2—grossly positive).To assess the effect of pneumoperitoneum pressure on tissue damage:Plasma damage-associated molecular patterns (DAMPs), for example, heat shock protein 70 (HSP70), high mobility group box 1 (HMGB1), nuclear deoxyribonucleic acid (nDNA), and mitochondrial DNA (mtDNA).Plasma cytokines (for example, tumor necrosis factor alpha (TNFα), interleukin-10 (IL-10), and IL-6) will be evaluated from blood samples drawn directly before the parenchymal phase and at the end of it, as well as on postoperative days 1 and 3.In addition, liver and peritoneal biopsies will be taken before and after the parenchymal transection phase of the liver resection. Biopsies will be used to extract mRNA and determine:Levels of hypoxia-inducible factor 1-alpha (HIF1α), TNFα, IL-1β, IL-6, vascular endothelial growth factor (VEGF), hepatocyte growth factor (HGF), and platelet-derived growth factor (PDGF).
